### Data collection

3.3

Data collection includes a range of methods, including biological sampling, quantitative surveys, qualitative interviews, ethnography field notes, participant observation, informal conversations, and in-depth interviews.

#### Quantitative data

3.3.1

Human participants will complete questionnaires that document potential risk factors associated with the carriage of resistant bacteria, including demographics, dietary patterns, recent AMU, animal contact, access to water and sanitation, and medical history. Farmers will provide information on flock management, biosecurity measures, AMU in farm, vaccination, and disease history. Data collection tools, ODK digital surveys [40], will be developed in the local language (Javanese and Bahasa Indonesia) and will be collected by the local Indonesian research team and pre-tested with local research assistants for clarity and cultural appropriateness. Human rectal swabs and poultry boot samples will be transported under a cold chain to the laboratory for processing within 24 h.

#### Qualitative data

3.3.2

Understanding the human behaviors and social factors driving AMU is critical in tackling AMR. COINCIDE integrates ethnographic approaches, including participant observation, informal conversations, in-depth interviews with key stakeholders (healthcare providers, pharmacists, technicians, public health workers, midwives, village cadres, farmers, veterinarians, and community members), and the participatory “drug bag” method interviews adapted from Dixon et al (2019) [41] to document household and farm antimicrobial usage, recognition and accessibility at community level. Simulated patient visits to pharmacies and local shops (*warung* or *toko obat*), along with interviews at agrovet shops will assess compliance with regulations governing antimicrobials, particularly colistin sales, that can reveal potential gaps in policy enforcement. Topic guides will be developed in an iterative manner. Qualitative data will be analyzed thematically and integrated with quantitative results to have a comprehensive understanding of macro-, meso-, and micro-level contextual factors influencing antimicrobial use and resistance in Indonesia.

### Laboratory protocols

3.4

Laboratory protocols will be developed iteratively in collaboration with local laboratories, given options for capacity building and limited resources available. Human rectal swab and poultry/environmental boot swab samples will be cultured for *E. coli* on MacConkey agar. For human isolates, bacterial identification will be done using an automatic machine (VITEK® 2 COMPACT, bioMerieux). One presumptive *E. coli* colony per human sample and 15 *E. coli* isolates from boot swabs from layer farms will be selected. For animal isolates, *E. coli* isolates will be confirmed using biochemical tests. In parallel, isolates will be plated on CHROMagar™ COL-APSE (selective medium) in a tailor-made spot-test protocol that allows screening up to eight isolates per plate to screen for colistin-resistant growth. The protocol has been published on https://www.protocols.io, and the video protocol is available online (https://youtu.be/KC1x9u4d02g). Each batch of CHROMagar plates will include a colistin-susceptible *E. coli* strain (ATCC 25922) and a known *mcr*-1-positive *E. coli* as negative and positive controls, respectively. All isolates that grow on CHROMagar (presumptive colistin-resistant) will be tested using automated broth microdilution system (Sensititre, ThermoFisher) to determine colistin MIC, following the most recent EUCAST/CLSI standards. MIC results will be interpreted using the EUCAST MIC and ECOFF database. The ECOFF for colistin resistance in *E. coli* is ≤2 mg/L [42]. All isolates will be catalogued and stored at −80 °C in laboratories in Indonesia. Colistin-resistant *E. coli* isolates will be sequenced using Oxford Nanopore Technologies (ONT) long-read sequencing. DNA extraction, library preparation, and sequencing will be performed in-country by trained local staff. Where relevant, the Microbiology Investigation Criteria for Reporting Objectively (MICRO) framework will be followed in reporting [43].

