**Methods and analysis:**

COINCIDE will: (i) assess phenotypic and genotypic colistin resistance in *E. coli* from humans and poultry; (ii) estimate transmission of colistin resistant *E. coli* between humans and animals; (iii) explore colistin and antimicrobial use (AMU) at the community level; (iv) identify social and cultural factors driving AMU; and (v) strengthen multisectoral One Health collaboration. Post-ban sampling will be conducted in three districts of Central Java Province (Klaten, Karanganyar, and Sukoharjo), where pre-ban samples were already available. We will recruit participants from primary healthcare centers (PHC) (*n* = 683), poultry farmers (*n* = 120), and visit a total of 60 small-scale layer farms. Broiler isolates (*n* = 2865) from Indonesia's routine antimicrobial resistance (AMR) surveillance (2018–2023) will also be included. In terms of sample collection, post-ban samples will include rectal swabs from patients visiting PHC and farmers and boot swabs from small-scale layer farms. Colistin resistance will be screened using CHROMagar COL-APSE agar medium and confirmed by broth microdilution. Results of long-read whole-genome sequencing will identify resistance mechanisms and transmission pathways. A qualitative ethnography work will include participant observation and informal conversations during field visits, alongside in-depth interviews with healthcare professionals and stakeholders. “Drug bag” method interviews will assess antimicrobial use, access, and drivers at the community level. Simulated patient visits to pharmacies and local shops (*warung* or *toko obat*), and interviews with agrovet outlets and poultry shops will be conducted to evaluate compliance with antimicrobial sales regulations.

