### Sample size and sampling strategies

3.2

To detect a meaningful reduction in colistin resistance from an estimated 15% before the ban to 10% afterward, power calculations indicated the need to analyze at least 683 *E. coli* isolates and risk factor surveys from both human and poultry sources. The retrospective (pre-ban) isolates include 577 archived human isolates from primary health care centers (PHC), 2182 broiler surveillance isolates, 513 layer chicken isolates, and 63 layer farmer isolates from 2014. Regarding the prospective sampling, human participants (*n* = 683) will be recruited from PHC, with eligibility criteria including adults over 18 years without current diarrhea or vomiting, who provide informed consent for rectal swab collection. Random selection via raffles of clinic attendees meeting these criteria will be used to minimize selection bias.

Up to 60 small-scale laying hen farms will be sampled to get an estimated 683 bacterial isolates, identified through local livestock office records. The small-scale layer farm is defined as having fewer than 10,000 layer chickens. Boot swabs will be collected from poultry houses. Farm workers (two or three from each farm, *n* = 120) will also be invited to provide rectal swab samples, enabling paired human-animal analysis. We will document recruitment and refusal rates in each setting to assess potential selection bias. All field teams will follow standard operating procedures developed by the COINCIDE consortium for sample labeling, cold-chain maintenance, and data recording to ensure quality and traceability. Additionally, available AMR data from the national broiler surveillance program from 2018 to 2023 will be incorporated. Within this surveillance program, approximately 800 caecal samples are collected from broilers per year via regional Disease Investigation Centers. From these samples, *E. coli* is isolated, and these isolates are tested for antimicrobial susceptibility including colistin using broth microdilution. These data provides a national perspective on resistance trends before and after the ban.

The complete COINCIDE sample scheme is also illustrated in Fig. 3.

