### Data management plan and data analysis

3.6

All data will be securely stored using the Yoda database and ODK data collection forms [40]. Personal identifiers will be pseudonymized or removed to preserve confidentiality. These data will only be available exclusively to principal investigators and data collectors. We will conduct periodic data audits and cleaning to ensure completeness and accuracy. Qualitative data will be analyzed using NVivo version 14. Genomics data will be analyzed using the command line and public bioinformatics resources, where available. All statistical analyses will be carried out using appropriate software such as R version 4.2.3, with a significance level of 0.05, adjusted for multiple testing, applied throughout unless otherwise specified.

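### PHC recruitment of 683 people with one colony per swab meets the stated minimum of 683 E. coli isolates only if every swab yields confirmed E. coli

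*Protocol article*

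**What the plan says.** Section 3.2 (Sample size and sampling strategies) plans for a fall in colistin resistance "from an estimated 15% before the ban to 10% afterward" and reports that "power calculations indicated the need to analyze at least 683" E. coli "isolates and risk factor surveys from both human and poultry sources". The same section sets post-ban human participants at n = 683, who "will be recruited from PHC, with eligibility criteria including adults over 18 years without current diarrhea or vomiting". The abstract gives the same recruitment figure. The pre-ban PHC comparator is 577 archived isolates. A further 120 farm workers give rectal swabs for a paired human-animal analysis, and there are 63 layer farmer isolates from 2014.

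Section 3.4 (Laboratory protocols) selects one presumptive E. coli "colony per human sample and 15" isolates from layer-farm boot swabs. On species confirmation it says: "For human isolates, bacterial identification will be done using an automatic machine" (VITEK 2). Section 3.6 sets tests "with a significance level of 0.05, adjusted for multiple testing". The article gives no recovery rate for E. coli from rectal swabs and does not state the power or sidedness behind 683.

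**The concern.** The requirement is written in isolates and the recruitment in people, and the same number serves for both. A person becomes an isolate only if the swab survives transport, grows, and gives a colony that is confirmed as E. coli. With one colony per person and no surplus of people, the plan reaches its own minimum only if this succeeds every time.

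At stake is the agreement between the sample size the article claims and the one its design delivers for the PHC before/after comparison. The pre-ban side of that comparison is a fixed archive that new sampling cannot enlarge, so the post-ban count is the only side the sponsor can still influence.

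**Working it through.** **Inputs.** Section 3.2: p1 = 0.15, p2 = 0.10, minimum 683 isolates, 683 PHC recruits, 577 pre-ban PHC isolates. Section 3.4: one colony per human sample. Section 3.6: alpha 0.05. Two-sided testing and 80% power are inferred from the match in step 1. Recovery rates are assumptions.

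**1. Reproducing 683.** Two independent proportions, unpooled variance, equal groups:

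n = (1.960 + 0.842)² × (0.15 × 0.85 + 0.10 × 0.90) / 0.05² = 682.85, rounded up to 683 per group.

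The pooled-variance version gives 686. Two-sided 90% power gives 915 (unpooled), and one-sided 80% gives 538. The match with two-sided 80% is exact and leaves no room for a hidden loss allowance.

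**2. One total or a number per source?** PHC participants are set at 683, layer isolates at an estimated 683, and the broiler counts differ by 683 (2865 in the abstract − 2182 in Section 3.2). The figure is used per source.

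**3. Maximum yield.** 683 people × 1 colony = 683 isolates, a margin of zero. One failed swab gives 682. At an assumed 99% recovery, the chance that all 683 succeed is 0.99^683, about 0.1%.

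**4. Power.** Unpooled, two-sided 0.05:

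power = Φ(0.05 / √(0.1275/577 + 0.09/n2) − 1.96)

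At n2 = 683 the standard error is 0.01878, so z = 0.702 and power is 75.9%.

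| Assumed recovery | PHC isolates (n2) | Power against 577 | Loss from full recovery |
|---|---|---|---|
| 100% | 683 | 75.9% | – |
| 95% | 649 | 75.1% | 0.8 points |
| 90% | 615 | 74.2% | 1.7 points |
| 80% | 546 | 72.1% | 3.8 points |

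**5. Splitting the gap from 80%.** Moving from 683 v 683 (80.0%) to 577 v 683 (75.9%) costs 4.1 points before any swab fails. Recovery loss adds 0.8, 1.7 or 3.8 points. At 95% and 90% the archive accounts for most of the gap; at 80% the two contributions are about equal. The pooled formula shows the same pattern (76.6%, 75.5%, 74.3% and 71.6%).

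**6. Multiplicity.** The figures use an unadjusted 0.05. The adjustment in Section 3.6 could only lower them; it is not quantified here.

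**The case against.** The strongest objection is that the practical effect is small. At 90–95% recovery the cost is under 2 points of power, and the larger shortfall comes from the 577 archived isolates, which has nothing to do with colony picking. This stands. A reader who set 75%, 74% or 72% against 80% might blame the whole difference on lost swabs; step 5 shows that would be wrong.

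A reader might also infer that the plan forbids a second pick when the first colony fails identification. It does not say so. Section 3.4 states that one colony is selected, is silent on failed identification, and says that laboratory protocols will be developed iteratively. Nor does Section 3.2 say that a failed swab cannot be replaced by another recruit, so it goes too far to say that 683 isolates cannot be reached in practice. What remains is that the three printed figures (isolates needed, people recruited, colonies per person) leave no margin. Even unlimited re-picking cannot give more than one isolate per person, or more than 683 in all.

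The 120 farm workers might seem to supply slack: 683 + 120 = 803 swabs would allow recovery to fall to about 85% (683/803). But Section 3.2 uses them for paired analysis and lists pre-ban farmer isolates separately, and pooling them would mix occupationally exposed people with clinic attendees.

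The layer sample may have a surplus, but this is less certain than it looks. It is 60 × 15 = 900 only if 15 means per farm and all of the up to 60 farms are visited. The point does not rest on that contrast.

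Finally, it would be too strong to call the prevalence denominator unclear. Section 3.2 counts both the requirement and the pre-ban set in isolates. Saying explicitly that confirmed isolates are the denominator is a clarification.

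**Conclusion.** The point holds as an inconsistency between figures the article itself states. The minimum number of analysed isolates is an uninflated per-group size, and PHC recruitment is set at that same number with one colony each, so the minimum is met only at 100% recovery. The consequence is modest: about 1 to 4 points of power at assumed recovery of 95% to 80%, on top of the 4.1 points already lost to the archive. The conclusion rests on reading 683 as a requirement per source, on the inferred two-sided 0.05 and 80% power, and on keeping farm workers as a separate stratum. The recovery rates are illustrative, and nothing in the article favours one of them. It is worth correcting because the stated size is not what the design delivers and the correction is cheap.

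**What to change.** **Section 3.2.** Describe 683 as the number of PHC participants recruited. State the expected number of confirmed isolates as 683 × an assumed recovery rate, with the source of that rate. Restate the power against 577 on that number; the table above gives the values. Name confirmed E. coli isolates as the prevalence denominator, as in the pre-ban set.

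**Section 3.4.** If the first presumptive colony is not confirmed as E. coli, pick the next colony in order from the same MacConkey plate and keep the first confirmed one. This still gives one isolate per person. MacConkey agar contains no colistin, so the rule does not select on resistance. Note that it rescues only misidentified colonies, not culture-negative or spoiled swabs, and that it may differ from the picking rule used in 2014.

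**Cost.** Some wording and a few extra identification tests on plates already cultured.

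**If 683 confirmed isolates is meant as a firm minimum,** these steps do not secure it. Recruitment would have to continue until that count is reached, or be inflated to 683/recovery: 719 at 95%, 759 at 90%, 854 at 80%. That adds fieldwork, and reaching 683 would still give only 75.9% power against the archive.

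### The only numeric criterion for colistin resistance points the wrong way: it attaches MIC ≤2 mg/L, the wild-type range, to resistance

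*Protocol article*

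**What the plan says.** Section 3.4 (Laboratory protocols) describes two steps. Isolates are first spotted on a colistin-selective agar. Then "All isolates that grow on CHROMagar (presumptive colistin-resistant) will be tested using automated broth microdilution system". The agar controls are a colistin-susceptible reference strain and "a known *mcr*-1-positive *E. coli* as negative and positive controls, respectively".

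On reading the MIC, the section says "MIC results will be interpreted using the EUCAST MIC and ECOFF database", and then gives the number: "The ECOFF for colistin resistance in *E. coli* is ≤2 mg/L". No other sentence in the article gives an MIC cut-off or says on which side of 2 mg/L resistance lies. Isolates classed as resistant then go to long-read sequencing.

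Section 3.2 (Sample size and sampling strategies) sizes the study on this outcome: "To detect a meaningful reduction in colistin resistance from an estimated 15% before the ban to 10% afterward", for which "power calculations indicated the need to analyze at least 683 *E. coli* isolates". It also says that the national broiler surveillance isolates are tested for colistin susceptibility by broth microdilution, and mentions no agar screen for them.

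**The concern.** An ECOFF marks the upper end of the wild-type MIC distribution. Isolates at or below it are wild type, and those above it are non-wild type. The sentence in section 3.4 names resistance and gives the wild-type side of the inequality. Taken as a coding rule, it would class as resistant the isolates that a low concentration of colistin inhibits.

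The cut-off sets the numerator of the prevalence named in the study's central question (section 2) and in the power calculation (section 3.2). It also decides which isolates are sequenced, and so which ones feed the work on resistance mechanisms and transmission. A published protocol is the reference for later reporting, so its only numeric definition of the outcome should not conflict with its own assay.

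**Working it through.** **1. Direction implied by the rest of section 3.4.**

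| Element of section 3.4 | Where resistance lies on the MIC scale |
|---|---|
| Growth on colistin agar is presumptive resistance | High end |
| Susceptible strain is the negative control | Susceptible means no growth, so resistance is at the high end |
| *mcr*-1-positive strain is the positive control | Resistant means growth, so resistance is at the high end |
| MICs read against the EUCAST MIC and ECOFF database | An ECOFF bounds the wild type from above, so resistance is above it |
| Cut-off sentence | At or below 2 mg/L: low end |

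Four elements agree and the cut-off sentence is the exception. The first three rows show the contradiction from the article alone.

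**2. Consequence of the literal reading, prospective human and layer isolates.** Only isolates that grow on the agar receive an MIC. Let g be the share that grows, t the share that grows with MIC >2 mg/L, and f the share that grows with MIC ≤2 mg/L, so g = t + f.

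- Intended rule: prevalence = t.
- Literal rule: prevalence = f = g − t, the false positives of the screen. It cannot exceed g.

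With the planned post-ban rate and 683 isolates, t = 10% gives 683 × 0.10 = 68.3, about 68 confirmed resistant isolates. The literal rule would drop all of these and count 683 × f instead. The article gives no value for f, so no figure can be put on the resulting prevalence. If the screen had no false positives, it would be zero.

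**3. Consequence of the literal reading, broiler surveillance isolates.** Here no screen is described, so each isolate has an MIC. If p is the share above 2 mg/L, the literal rule reports 1 − p. Borrowing the planning rates purely as an illustration (the article does not give them as broiler rates):

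- before the ban: 1 − 0.15 = 0.85
- after the ban: 1 − 0.10 = 0.90

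A fall of 5 percentage points would appear as a rise of 5 points.

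**4. Effect on the sample size.** Inputs: 15% and 10% (section 3.2) and alpha 0.05 (section 3.6, Data management plan and data analysis). Two-sided testing, 80% power and equal groups are my assumptions, since the article does not state them. With unpooled variance:

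n per group = (1.960 + 0.842)² × (0.15 × 0.85 + 0.10 × 0.90) / 0.05² = 7.849 × 0.2175 / 0.0025 ≈ 682.9, rounded up to 683.

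This reproduces the article's figure. The pooled-variance version gives 686. Swapping to 85% and 90% leaves every term unchanged (0.85 × 0.15, 0.90 × 0.10, difference 0.05), so n is the same in either direction.

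**The case against.** The strongest reply is that the sentence does not say that isolates at or below 2 mg/L are resistant. It reports an ECOFF, and an ECOFF written as ≤2 mg/L is ordinary wild-type notation under a badly chosen label. The section makes the direction clear elsewhere and sends interpretation to the EUCAST database, so a trained microbiologist would code the isolates correctly. That stands as far as the practical risk goes: a wording slip is the likely cause and miscoding is improbable. It does not make the sentence right, because nothing else in the article states the criterion in the correct direction.

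Three stronger readings should be set aside.

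- A reader might infer that 15% resistance would be reported as 85% throughout, or that about 615 of the 683 post-ban isolates (90%) would be called resistant. The workflow rules this out for the prospective isolates: those that do not grow on the agar never reach the MIC rule.
- A reader might infer from "following the most recent EUCAST/CLSI standards" that two bodies' cut-offs are in play. That phrase governs how the MIC is determined. Interpretation is a separate sentence and names EUCAST alone.
- A reader might infer that the plan allows different cut-offs before and after the ban. The article gives one value and nowhere says that it changes. How MICs from different years are harmonised is detail that an article may leave to the full protocol.

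**Conclusion.** The point holds as an error of direction in the stated decision threshold. Section 3.4 attaches the wild-type side of 2 mg/L to resistance and so contradicts its own screening step and controls. Taken literally, the rule would keep only the false positives of the screen among prospective isolates and would swap the two classes in the surveillance isolates.

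The size is limited. The documents give no ground to question the value 2 mg/L. The sample size of 683 is the same in either direction. Actual misclassification is unlikely given the reference to the EUCAST database. The article does not use the term primary outcome. The weight of the point rests on colistin resistance being the subject of the central question and of the power calculation. The surveillance consequence assumes that those isolates are read with the section 3.4 cut-off and, as section 3.2 describes, without a prior screen.

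The sentence should be corrected. The design and the planned analysis stand as they are.

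**What to change.** Replace the cut-off sentence in section 3.4 with: *Isolates with colistin MIC >2 mg/L are classified as colistin-resistant (non-wild type); MIC ≤2 mg/L is wild type (ECOFF 2 mg/L).*

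The cost is one sentence, with no change to sampling, laboratory work or sample size. As an optional clarification, the sponsor could add that the same cut-off is applied to pre-ban, post-ban and surveillance MICs. Its absence is not an error in the plan.
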